### *3.3.2 Standard care*

Fluid may be given intravenously in amounts of the clinician's choice as usual. There will be no upper limit for the use of either IV or oral/enteral fluids. In particular:

- IV fluids should be given in the case of hypoperfusion or circulatory impairment and should be continued as long as hemodynamic variables improve as chosen by the clinicians. These criteria are based on the SSC guideline
- IV fluids should be given as maintenance if the departments have a protocol recommending maintenance fluid
- IV fluids should be given to substitute expected or observed loss, dehydration or electrolyte derangements

### *3.3.3 Co-interventions*

Types of fluids in both intervention groups:

- Fluids used for electrolyte disturbances: Fluids should be chosen to substitute the specific deficiency
- Fluids given to substitute overt loss: Isotonic crystalloids are to be used. If large amounts of ascites are tapped, then human albumin may be used.
- Blood products are only to be used on specific indications including severe bleeding, severe anaemia and prophylactic in case of severe coagulopathy.

### *3.3.4 Concomitant interventions*

Patients should, besides the above-mentioned randomized treatments, be cared for as usual in terms of their infection. Treatment of sepsis is complex with multiple interventions and, as blinding of treating personnel is not feasible, use of several concomitant interventions may be influenced by allocated intervention arm. In order to minimize these potential differences, the use of concomitant interventions for sepsis should be based on the Danish Society of Infectious Disease guidelines and the one-hour bundle from SSC.

### *3.3.5 Criteria for modification of interventions for a given trial participant and protocol violations*

The clinical team may at any time violate the protocol if they find it to be in the interest of the participant. We will have a 24-hour per day trial hotline to enable discussion between the clinicians caring for trial participants and the REFACED Sepsis trial team regarding protocol related issues.

Protocol violations are defined as follows:

| Intervention group               | Major protocol violation                                                                                                                                                                                                                                                                                                                                                        | Documentation                      |
|----------------------------------|---------------------------------------------------------------------------------------------------------------------------------------------------------------------------------------------------------------------------------------------------------------------------------------------------------------------------------------------------------------------------------|------------------------------------|
| Restrictive fluid administration | IV fluids given if none of the bellow is true: 

• 1 or more hypoperfusion criteria fulfilled

• To correct documented fluid loss

• To correct significant electrolyte deficiencies

• Fluid administered as carrier for medication (e.g. antibiotics)

• Ensure a total fluid input of 1 L per 24 h

 | Reasons for the protocol violation |
| Standard care                    | No IV fluids given                                                                                                                                                                                                                                                                                                                                                              | Reasons for the protocol violation |

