#### 3.3 Interventions

##### 3.3.1 Restrictive fluid administration

No IV fluids should be given unless one of the below mentioned occurs; in these cases, IV fluid may be given in measured amounts:

A fluid bolus of 250 ml (half of a 500 ml fluid bag) isotonic crystalloid may be given within 15 minutes if one of the following occurs (hypoperfusion criteria):

- Lactate concentration  $\geq 4$  mmol/l (arterial or venous blood gas/blood sample)
- Hypotension (systolic BP  $< 90$  mmHg)
- Mottling beyond edge of kneecap (i.e., Mottling score  $>2$ )
- Severe oliguria, i.e., diuresis  $< 0.1$  ml/kg/h, during the first 4 hours of admission

The effect of a fluid bolus may be assessed after 30 minutes by re-evaluation of the four hypoperfusion criteria mentioned above by the treating clinician. If one or more of the criteria are still fulfilled, a fluid bolus as defined above may be repeated. At any time, the clinician can start vasopressors if deemed necessary.

Only isotonic crystalloids are to be given as resuscitation fluid; the type of isotonic crystalloid is free of choice. Crystalloid boluses are to be given via IV drip. Intravenous fluids may be given as carrier for medication, but the volume should be reduced to the lowest possible volume for the given medication.

In case of documented overt fluid losses (e.g., vomiting, large aspirates, diarrhea, drain losses, or ascites drainage or due to dehydration) IV fluid may be given to correct for the loss.

In case the oral/enteral route for water or electrolyte solutions is contraindicated or has failed as judged by the clinical team, IV fluids may be given to:

- Correct significant electrolyte deficiencies
- Ensure a total fluid input of 1 L per 24 h (fluids with medications and nutrition count as input).

If a patient undergoes surgery during the 24 hours inclusion period, they are temporarily out of the protocol, but we will encourage continuing restrictive fluid therapy.

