The cut-off value of lactate was chosen based on SSC guidelines and their one-hour bundle and data indicating that the marked increase in mortality occur at lactate values above 4 mmol/l. The mottling trigger is based on mottling score  $\geq 2$  (see figure below) as described by Ait-Oufella et al and validated in a pre-hospital setting. Severe oliguria is defined as urine output  $\leq 0.1$  ml/kg/hour and the criteria is only to be used within the first 4 hours of admission.

[figure not shown]

Figure showing Mottling score, copy with permission from Ait-Oufella et al.

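### The major-violation definition omits the oral-route condition of section 3.3.1, so it undercounts restrictive-arm violations; the mottling trigger it relies on is stated two ways

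*Protocol*

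**What the plan says.** Section 3.3.1 opens the restrictive regimen with a prohibition: "No IV fluids should be given unless one of the below mentioned occurs". It then lists the exceptions. Two of them, correcting significant electrolyte deficiencies and bringing total input to 1 L per 24 hours, stand under one introductory condition: "In case the oral/enteral route for water or electrolyte solutions is contraindicated or has failed as judged by the clinical team".

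The table in section 3.3.5 (the section on modification of interventions and protocol violations) is introduced with "Protocol violations are defined as follows". For the restrictive arm, IV fluid is a major violation only if none of five reasons applies. Two of the five are "To correct significant electrolyte deficiencies" and "Ensure a total fluid input of 1 L per 24 h". Neither row carries the oral-route condition, and the table does not refer back to 3.3.1. No minor category is defined.

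A third excusing reason is that at least one hypoperfusion criterion is met. For mottling, the treatment list in 3.3.1 says "Mottling beyond edge of kneecap (i.e., Mottling score" and gives a score above 2. The rationale later in the same section says "The mottling trigger is based on mottling score" and gives 2 or more. The oliguria limit also changes, from strictly below 0.1 ml/kg/h in the list to 0.1 or below where the rationale says "Severe oliguria is defined as urine output".

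**The concern.** The table fixes how an outcome is counted, and it does not match the treatment rule whose adherence it measures. The number of patients with major protocol violations is a secondary feasibility outcome in section 5.2.1. The Overview and section 3.1 list protocol violations among the key secondary outcomes, and section 6.2.1 promises to report them as a feasibility measure. The trial is meant to inform a decision on a large-scale trial (sections 1.3 and 9.1), so how well clinicians kept to the restrictive regimen is one of its main products.

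If the definition excuses fluid that the regimen forbids, adherence will look better than it was. Two assessors, one applying the table and one carrying over the condition from 3.3.1, could also classify the same patient differently. The two mottling cut-offs raise the same classification problem and leave clinicians with two thresholds for giving a bolus.

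**Working it through.** The protocol gives no figure to reproduce on this point. The check is a comparison of texts, followed by simple arithmetic on the possible size.

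**Step 1. The two rules side by side (restrictive arm).**

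| Reason for IV fluid | Section 3.3.1 | Table in 3.3.5 |
|---|---|---|
| Electrolyte correction | Allowed only if the oral/enteral route is ruled out or has failed | Excused, no condition |
| Reaching 1 L total input | Allowed only if the oral/enteral route is ruled out or has failed | Excused, no condition |
| Mottling score exactly 2, no other reason | Not a trigger in the list (above 2); a trigger in the rationale (2 or more) | Excused if a hypoperfusion criterion is met, so it depends on which text is used |

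**Step 2. Direction.** On the first two rows the table excuses everything 3.3.1 permits, and more. Patients counted as violators under the table are therefore a subset of those who would be counted with the condition in place. The restrictive-arm count can fall but not rise. The standard-care definition (no IV fluid given) is untouched.

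**Step 3. Who is missed.** Let k be the number of restrictive-arm patients whose only breach is electrolyte or 1 L fluid given although the oral route was usable. A patient with some other unexcused infusion is counted under either rule and does not add to k. The 1 L row partly limits itself: if oral intake counts toward total input, someone already drinking 1 L needs no IV fluid to reach it. The exposed cases are patients able to drink who take in less than 1 L, and electrolyte deficits that could have been treated orally.

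**Step 4. Size.** Section 6.1 plans 62 patients per arm. Understatement of the restrictive-arm violation rate = k/62.

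| Assumed k | k/62 | Percentage points |
|---|---|---|
| 0 | 0 | 0 |
| 1 | 0.0161 | 1.6 |
| 3 | 0.0484 | 4.8 |
| 6 | 0.0968 | 9.7 |

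These values of k are illustrations; nothing in the protocol allows k to be estimated.

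**Step 5. Can it be repaired from the data?** Sections 7.1 and 7.1.6 record an indication for each bolus, and section 7.1 also records violations with their reasons. No listed variable records whether the oral route was usable. The data dictionary announced in section 7.1.2 might add one, but it is not shown.

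**Step 6. What is not affected.** The primary outcome is a volume and does not use the violation definition. The sample size is likewise independent of it: with a difference of 1 L, SD 1.7 L, two-sided alpha 5% and power 90%, the exact t-test requires 61.7 per arm, rounded to 62 (124 in total, power 90.1%), as section 6.1 states.

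**The case against.** The best defence is that the table is shorthand for 3.3.1. It also leaves out the 250 ml bolus size, the re-evaluation step and the lowest-carrier-volume rule, and its hypoperfusion row cannot be applied without going back to 3.3.1. On that reading the 1 L row means the 1 L allowance as already defined. But the table keeps other qualifiers (fluid loss must be documented, electrolyte deficiencies significant), drops this one, and contains no cross-reference. A reader may supply the condition; the text does not require it.

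A second defence is that a major category may legitimately be narrower than every departure from the regimen. That would be reasonable if the protocol said so. The lead-in presents the table as the definition of protocol violations generally, and no lesser category exists to catch what it leaves out.

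Several points do stand:

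- Oral-route failure is a bedside judgement, and a clinician who records the 1 L indication has often already judged oral intake inadequate. Section 9.2.3 also excludes patients able to consent, so many of those enrolled may truly be unable to drink. Both suggest k could be small.
- For mottling, the treatment list is the operative text and is anchored to an anatomical landmark; the other cut-off is in a rationale paragraph.
- The protocol sets no violation threshold or go/no-go rule, so no stated decision turns on this count.

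These points limit the likely effect. They do not reconcile the definition with the rule.

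**Conclusion.** The concern holds. As written, the major-violation definition excuses two uses of IV fluid that section 3.3.1 forbids when the oral route is usable, so it understates restrictive-arm violations by k/62. The direction is certain; the size is unknown and may be zero. The percentages assume that all 62 planned patients are in the denominator and that assessors apply the table literally.

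The mottling inconsistency is real but narrower. It matters only for boluses given for a score of exactly 2 with no other listed reason. The difference in the oliguria sign has negligible effect.

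This should be corrected because it concerns a named outcome and a bedside threshold and costs almost nothing to repair. It does not threaten the primary analysis.

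**What to change.** - In the section 3.3.5 table, add to the electrolyte and 1 L rows that they apply only when the oral/enteral route is contraindicated or has failed.
- Add a yes/no box for that judgement to the bedside chart.
- Use one mottling cut-off throughout section 3.3.1. The list's version (score above 2, beyond the kneecap) is the natural choice. Align the oliguria sign at the same time.
- If charts are already in use without the box, report two restrictive-arm counts: one with the table as written (lower bound), and one treating all electrolyte and 1 L fluid as violations (upper bound). The upper figure will include fluid that 3.3.1 permits, so it bounds this issue and is not an estimate.
- Optionally, state that fluid given during surgery is not counted, as 3.3.1 already implies by placing those patients temporarily outside the protocol.

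The cost is rewording two table rows, aligning the rationale with the list, and adding one tick box. The box adds a little recording work and rests on clinical judgement, and the recorded violation count may rise.

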### *3.3.5 Assessment of participant compliance*

We will monitor protocol compliance at the trial site through the electronic case report form (eCRF) in REDCap and alert sites in the case of clear violation (central monitoring). In addition, the trial will be monitored according to the Good Clinical Practice (GCP) directive and a monitoring plan conducted in collaboration with the GCP-unit at Aarhus and Aalborg Universities.

## **3.4 Blinding**

Fluid restriction vs. standard care fluid therapy cannot be blinded for investigators, clinical staff, or participants.

## **3.5 Trial procedures**

### *3.5.1 Patients*

The trial procedures will be limited to the interventions given in the first 24 hours of admission. Data will be obtained from the study specific case report form and the electronic medical records.

### *3.5.2 Clinical personnel*

Prior to the beginning of patient enrollment and continuously throughout the enrollment period, the clinical teams involved in the treatment of sepsis patients at the participating hospitals will be informed about the

trial. Clinical personnel will be informed about the background and objectives of the trial, the inclusion/exclusion criteria, the interventions, and the trial procedures they are involved in. We anticipate formal, in-person didactics continuously with informal sessions and emails as applicable in between as well as an educational video, especially due to the current COVID-19-pandemic.

## **4. SETTING AND PATIENT POPULATION**

### **4.1 Setting**

The trial will be conducted at three EDs at Aarhus University Hospital and Regional Hospital Randers and Viborg, Denmark. All three participating sites have clinical experience and expertise in treating sepsis patients.

### **4.2 Inclusion criteria**

The research team, clinically working nurses and ED physicians will screen ED patients for the following inclusion criteria:

- 1) Unplanned emergency department admission
- 2) Age  $\geq 18$  years
- 3) Sepsis defined as
  - a) suspected infection by the treating clinician AND
  - b) blood cultures drawn AND
  - c) IV antibiotics administered or planned AND
  - d) An infection related increase of SOFA-score  $\geq 2$  from baseline
- 4) Expected hospital stay > 24 hours as deemed by treating clinician

These broad inclusion criteria were chosen to investigate the effect of fluid administration in the entire, broad sepsis population and increase the likelihood of describing the entire 24 hours inclusion period. We will strive to enroll participants as soon as they fulfill the criteria in the ED. There is no exact maximum time frame for patient inclusion, however with the exclusion criteria of > 500 ml. IV fluids administered, the inclusion is expected and intended to happen within the first couple of hours.

### **4.3 Exclusion criteria**

We will exclude patients fulfilling any of following exclusion criteria:

- 1)  $\geq 500$  ml of fluids given prior to randomization
- 2) Invasively ventilated or vasopressors initiated at the time of screening
- 3) Known or suspected severe bleeding judged by the treating clinician
- 4) Known or suspected pregnancy (women aged  $<45$  years will have a pregnancy test performed before enrollment)
- 5) Prior enrollment in the trial
- 6) Patients, who the clinician expect not to survive the next 24-hours

#### **4.4 Co-enrollment**

There will be no general restrictions on entry into other clinical trials although this will be evaluated on a case-by-case basis. However, patients enrolled in REFACED Sepsis will not be able to be enrolled in the CLASSIC trial (ClinicalTrials.gov identifier NCT03668236) if transferred to the ICU, since it would be contradictory to receive restrictive care in one of the studies and standard care in the other at the same time.

### **5. OUTCOMES**

#### **5.1 Primary outcome**

##### *5.1.1 Definition*

The primary outcome will be the total amount of all administered intravenous, crystalloid fluids within 24 hours of randomization.

##### *5.1.2 Feasibility aim*

The primary result is to see, if patients in the restrictive arm have significantly less intravenous fluid administered within 24 hours than the standard-care group. This study is a feasibility study, and a future large-scale study is planned.

#### **5.2 Secondary outcomes**

##### *5.2.1 Definitions*

The secondary outcomes will be

- Feasibility measures:
  - Number of patients with major protocol violations,

- Number of patients screened positive (ie.with all inclusion criteria fulfilled and no exclusion criteria fulfilled) vs randomized
- Time from admission to inclusion
- Number of patients lost to follow up in terms of 24-hour fluids (e.g. due to discharge within 24 hours)
- Accumulated serious adverse reactions and events (SAEs + SARs+ SUSARs) within 7 days in-hospital
- Total fluids (oral and intravenous) at 24 hours

We will also report in-hospital mortality and 30- and 90-day mortality (possible outcomes for the final large scale trial), in-hospital length of stay (LOS), mechanical ventilation within 7 days of admission (yes/no), vasopressor use within 7 days of admission (yes/no), and development or worsening of acute kidney failure according to the KDIGO3-criteria within 7 days of admission (also an SAE, see above) .

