| Recruitment status      | Planning                                                                                                                                                                                                                                                                                                                                                                                                                                                        |                              |
| Primary outcomes        | 24-hour intravenous crystalloid fluid administration                                                                                                                                                                                                                                                                                                                                                                                                            |                              |
| Key secondary outcomes  | Feasibility measures: 
 
• Number of patients with major protocol violations,
 
• Number of patients screened vs included
 
• Time from admission to inclusion
 
• Number of patients lost to follow up in terms of 24-hour fluids
 
• Accumulated serious adverse reactions and events (SARs + SUSARs) within 48 hours in-hospital
 
 Total fluids (oral and intravenous) at 24 hours, |                              |

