#### *5.4.2 Definitions for adverse events and reactions*

The following definitions will be used:

Adverse event (AE): any untoward medical occurrence in a subject to whom a medicinal product is administered and which does not necessarily have a causal relationship with this treatment

Adverse reaction (AR): All untoward and unintended responses to an investigational medicinal product related to any dose administered

Serious adverse event (SAE): Any adverse event that results in death, is life-threatening, requires hospitalization or prolongation of existing hospitalization, results in persistent or significant disability or incapacity, or is a congenital anomaly or birth defect.

Serious adverse reaction (SAR): Any adverse reaction that results in death, is life-threatening, requires hospitalization or prolongation of existing hospitalization, results in persistent or significant disability or incapacity, or is a congenital anomaly or birth defect. The SARs are identified in the Danish Summary of Products Characteristics (SmPC) for the used crystalloids.

Suspected unexpected serious adverse reaction (SUSAR): a serious adverse reaction, the nature, severity or outcome of which is not consistent with the reference safety information (SmPC).

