#### *5.4.3 Assessment of adverse events*

##### *Timing*

In all participants, we will assess the occurrence of SARs in the 7 days following randomization (the intervention period is 24 hours; 7 days allow for another 6 days of assessment after the intervention, which is clinically relevant in critically ill patients).

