##### *Classification of an event*

We will make no inferences about a causal relationship between the intervention and the SARs but register the occurrence in the two groups and report them in the final report according to the definition given above. The investigators will classify SAEs (as per the definition above occurring within 7 days from randomization) and report them to the sponsor. If such a SAE is deemed both unexpected and related to the intervention by the investigator, it will be considered a SUSAR and reported as such. If the sponsor does not adjudicate the SAE as related to the intervention, this will also be noted in the final report to the Medicines Authorities.

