#### *7.1.7 Variables on every day until 7 days from enrollment*

On mechanical invasive ventilation or vasopressor Y/N

SAEs (see section 5.4.3 + see above)

SUSARs (see section 5.4.5)

Status: dead, Y/N

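### The composite harm outcome has three different windows, and the one in section 5.2.1 stops at discharge, so time at risk depends on length of stay

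*Protocol*

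**What the plan says.** The same harm outcome, or the data that feed it, is given a window in several places in the protocol:

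- Section 5.2.1 (secondary outcomes): "Accumulated serious adverse reactions and events (SAEs + SARs+ SUSARs) within 7 days in-hospital".
- Overview table, key secondary outcomes: "Accumulated serious adverse reactions and events (SARs + SUSARs) within 48 hours in-hospital". The window is shorter and SAEs are absent from the bracket.
- Section 5.4.3, Timing: "In all participants, we will assess the occurrence of SARs in the 7 days following randomization". The reason given is that this adds six days of assessment after the 24-hour intervention.
- Section 5.4.3, Classification: SAEs are those "as per the definition above occurring within 7 days from randomization".
- Section 7.1.7 is headed "Variables on every day until 7 days from enrollment". It lists SAEs, SUSARs and vital status, with no restriction to inpatients.
- Appendix 3 covers reporting from randomization to day 7, also without an in-hospital limit.

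Section 5.4.2 defines an SAE as "Any adverse event that results in death, is life-threatening, requires hospitalization or prolongation of existing hospitalization", among other criteria. Eligibility under section 4.2 includes "Expected hospital stay > 24 hours as deemed by treating clinician". Sections 5.2.1 and 6.2.3 both foresee that some participants will be discharged even within 24 hours.

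**The concern.** Section 5.4.1 says that overall benefit and potential harm will be captured by the secondary outcomes, and this is the only composite harm outcome among them. An analyst who follows 5.2.1 counts events up to day 7 or discharge, whichever comes first. Length of stay is measured after randomization, is itself a reported outcome, and is set by clinicians who know the allocation (section 3.4). If one arm goes home earlier, it has fewer days in which an event can count, so the comparison mixes harm with discharge practice.

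The events most exposed are serious by the protocol's own definition: a death at home, or an event that leads to a new admission ("requires hospitalization or prolongation of existing hospitalization"). Appendix 3 names heart failure, pulmonary edema and severe kidney injury among the expected SAEs, and any of these could bring a discharged patient back. The trial is meant to inform a large-scale trial, so its harm counts will be used.

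**Working it through.** **The plan's own figure.** No rate, size or power is stated for the harm outcome, so there is nothing to reproduce for it directly. The stated trial size does reproduce. With a difference of 1 L, SD 1.7 L, two-sided alpha 5% and power 90%, the exact two-sample t-test needs 61.7 per arm, so 62 per arm and 124 in total, with power 90.1%. That calculation concerns the fluid volume outcome and does not bear on this point.

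**The windows side by side.**

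| Place | Length | Starts from | In hospital only? |
|---|---|---|---|
| Overview | 48 hours | not stated | yes |
| 5.2.1 | 7 days | not stated | yes |
| 5.4.3 (SARs, SAEs) | 7 days | randomization | no |
| 7.1.7 (daily data) | 7 days | enrollment | no |
| Appendix 3 | to day 7 | randomization | no |

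The reported outcome is therefore narrower than the safety assessment it should summarize, and the Overview version is narrower again. Section 5.2.1 also pulls against itself. It reports KDIGO3 kidney failure within 7 days of admission, with no in-hospital limit, and notes that this is also an SAE. The same event after discharge could count there and not in the composite.

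**What is collected after discharge.**

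- Death: daily status to day 7 (7.1.7), then day 30 and day 90 (7.1.8). Later survival comes from medical records or the civil register (5.2.2).
- Readmission: not listed in any of sections 7.1.5 to 7.1.9.

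**What Table 1 can and cannot show.** Patients not admitted beyond 24 hours number 540 − 382 = 158, and 158/540 = 29.3%. By site the figures are 62/337 = 18.4% and 96/203 = 47.3%. These are unselected sepsis patients at a 24-hour cut. Inclusion criterion 4 selects against exactly those patients, and the table says nothing about discharge between day 1 and day 7.

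**Illustration of days at risk (assumed, because no length-of-stay distribution is given).** Suppose every stay lasts at least 1 day, followed by an exponential remainder. For median stay M, the mean remainder is m = (M − 1)/ln 2. Then:

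- share of the 7-day window spent in hospital = [1 + m(1 − e^(−6/m))]/7
- proportion discharged before day 7 = 1 − e^(−6/m)

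| Assumed median stay (days) | Discharged before day 7 | Share of 7-day risk time in hospital |
|---|---|---|
| 3 | 87.5% | 50% |
| 5 | 65% | 68% |
| 7 | 50% | 76% |
| 10 | 37% | 83% |

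For M = 3, for example: m = 2/0.693 = 2.885; e^(−6/2.885) = 0.125; share = (1 + 2.885 × 0.875)/7 = 0.50.

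**If the arms differ in stay.** Medians of 5 v 4 days give 0.607/0.676 = 0.90, about 10% less observed risk time in the shorter-stay arm. Medians of 5 v 3 days give 0.504/0.676 = 0.75, about 25% less. These are ratios of time observed. They become ratios of event counts only if daily risk is constant and equal in and out of hospital.

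**The case against.** The strongest reply is that the safety sections set a 7-day window from randomization in all participants, that daily SAE and SUSAR collection runs to day 7, and that one loosely worded bullet in 5.2.1 does not make a trial that discards events. That is largely fair for data capture. It does not settle what will be reported, because 5.2.1 is where the outcome is defined and the Overview gives yet another definition.

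Some stronger readings are tempting, and the document does not support them:

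- A reader might infer that post-discharge deaths are lost. They are not: daily status to day 7 and 30- and 90-day mortality are collected. Such deaths are at risk of being missing only from this composite.
- A reader might infer that readmissions are definitely excluded. A patient readmitted on day 5 is in hospital within 7 days, so the wording can be read either way. That is an ambiguity, not a stated exclusion.
- A reader might infer that discharged patients are scored as event-free. The protocol states no such rule.
- A reader might take 29% from Table 1 as the early-discharge rate. It is not, for the reasons shown in the check.

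Three further objections stand in part. If events cluster early, or patients fit for discharge are at lower risk, any distortion is smaller than the risk-time ratios suggest. Many listed SARs and SAEs need blood tests, imaging or endoscopy, so removing the in-hospital limit will not find them in untested patients at home. And length of stay is reported, so an imbalance in exposure would be visible to a careful reader.

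**Conclusion.** The point holds as an inconsistency in the definition of the only composite harm outcome, with a possible bias if 5.2.1 is followed literally. Three windows are in force at once, and the one in 5.2.1 ties time at risk to open-label discharge decisions. It can also leave out events that meet the protocol's SAE definition.

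The size cannot be computed from the document. The 50% to 83% range for observed risk time, and the 10% and 25% differences between arms, rest on an assumed distribution of stay and on assumed medians. Substantial discharge before day 7 is plausible with an expected stay above 24 hours as the only requirement, but it remains an assumption. This is a secondary outcome in a feasibility trial powered only for its primary aim; the primary analysis and the sample size are unaffected. The change is worth making because it is cheap and removes an avoidable source of bias.

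**What to change.** 1. In 5.2.1, delete the in-hospital restriction and count SAEs, SARs and SUSARs to day 7 after randomization, whether or not the patient has been discharged.
2. Align the Overview, 5.4.3 and 7.1.7 to that single window and starting point, and restore SAEs to the Overview bracket. Section 5.4.5, which counts SUSARs from admission, should use the same clock. Name SARs explicitly in 7.1.7, which at present lists only SAEs and SUSARs by name.
3. Use the day-7 death status already collected in 7.1.7 to complete the composite. No new death item is needed.
4. Add one item to 7.1.7: readmitted by day 7, with the reason, taken from the electronic medical record. State that this is how post-discharge events are found.

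The cost is a wording change and one record check per discharged patient at day 7, with no patient contact. Event counts will be slightly higher. Events that need hospital tests will still be missed in patients who are at home and not tested, and the report should say so.
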